### The Anonymous Third-Party Reporting (ATPR) method (or confidantes' method)

ATPR was developed to collect quantitative data on induced abortion in restrictive contexts, by asking survey respondents to report anonymously on the recent abortions which occurred to a set of close female relations previously listed, including details on the abortion procedure and the complications experienced. The ATPR method is based on ethnographic work in Burkina Faso showing that information on abortions circulates in social networks in spite of this practice being strongly stigmatized, because women and couples cannot access abortion services otherwise [11]: information sharing is restricted to close relations and to people who can help in accessing abortion services, i.e. other abortion seekers or abortions providers. The ATPR defined close relations as people with whom respondents exchange private (i.e. secret, intimate) information; only female relations aged 15–49 (the demographic reproductive age group)—who can have abortions- are listed. Whilst the first tests of this method in Burkina Faso and Zambia and recent applications in PMA2020 surveys have yielded plausible results [12–14], four limitations have persisted. (i) First, different biases can affect ATPR results: *transmission bias -*respondents sometimes do not know about the abortions of their close relations-, *barrier bias* -abortion seekers' social networks may differ from that of average women- and *selection bias* -close female relations may have different networks than the general population-Up until now, these biases have been corrected for in an unsystematic way: different propositions coexist [14–19]. (ii) Second, it remains unclear in which contexts these biases are low and ATPR is applicable and in which contexts it is not the case [15, 16]. The existence of a transmission bias can be ascertained a priori, through a qualitative study documenting whether women with unintended pregnancies talk to close network members to locate underground abortion services [20]; but selection and barrier bias can be detected only when applying the method, suggesting the need for a quantitative pre-test. A fourth bias -*social desirability-* (not wanting to report on network member abortion or in the opposite overreporting such events) [15, 21] could also be probed in a pre-test. (iii) Third, the ATPR results ideally need to be validated, internally or externally. (iv) Fourth, the best standardized and unbiased network-generating question remains to be identified, as mentions of abortion in the presentation of the survey or in the network-generating question itself has been shown to inflate the estimates, and as a question focused on “secret sharing” may -perhaps- inflate the responses [18].^3^

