In their 2016 publication [30] Feehan et al. report on the impact of asking respondents for information about a smaller network of relations (circa 100 people you ate a meal with, instead of circa 250 people you know), which bettered the quality of the information collected. The NSUM is therefore starting to go in the direction of the ATPR, which requests information about an intimate network of women. However, because close relations are a subset of all relations, *selection biases* will additionally need to be considered in the ATPR, as well as the independence of the network generating question versus the practice of interest. Nevertheless, ATPR has several advantages over the NSUM: only counts can be obtained with the NSUM, while details on the procedures can be collected via the ATPR. Second, the transmission bias is obviously much weaker in networks of close relations as opposed to circles of people you "know" or "ate a meal with". Accordingly, plausible data on abortion have been collected via ATPR in some places, while NSUM failed to do so. In this study we will thus apply the ATPR rather than NSUM. However, some features of NSUM can be used to improve on the ATPR, especially its systematic formula to correct for transmission and barrier biases and its attention to the issue of social desirability.

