##### Questionnaire

The questionnaire will include five sections.Sociodemographic characteristics and reproductive history of the respondent (including questions on her own abortions, towards the end of the interview).List of close network members, only females aged 15–49, with a standard network generator question from international social surveys and the shared secret question. Special care will be given to train fieldworkers and monitor them when administering this section, as interviewer effects have been identified in the literature for network generating questions.Characteristics of network members: sociodemographic characteristics (including whether in the area or not, since when in the area and since when a close relation), reproductive history, number and timing of any induced abortions in the past 3 years, how the abortion was induced (provider, setting, method), gestational age, post-abortion complications, treatment obtained for post-abortion complications, abortion related stigma, number of close relations by confidants. To maintain confidentiality, we will not collect information on relations' names but will ask them to provide nicknames or fictional names for each.Measures of abortion related stigma at the community level, personal level and internalized.

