##### Questionnaire

The questionnaire administered to RDS participants will include:Sociodemographic characteristics and reproductive history of the respondent.Abortion history including number and timing of any induced abortions, how the abortion was induced (provider, setting, method), gestational age, post-abortion complications, treatment obtained, stigma (to be skipped for non-abortion seekers in multiplex RDS)Questions to estimate the biases of the ATPR: apply the ATPR modules to count close relations, characteristics of close relations, whether they had abortions, whether they told the respondents, how it was induced and any medical sequelae. For abortion seekers the module also contains the following questions: whether these close relations know about their abortions (whether respondents told them directly, respondents suspect they know even when not told).Stigma: three stigma scales will be used: community level, personal attitudes and internalized.

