### Plans for analyses

The analyses will focus on the two network methods applied to measure abortion safety (RDS and ATPR). The ATPR and RDS will provide data on what methods women use to have an abortion, where they have abortions and with what kind of provider, what side effects and post abortion care seeking behaviours they report.

The *RDS data* will be analyzed using the Respondent-Driven sampling analysis tool (RDSAT) or alternative tools in Stata or R, modified to take into account the multiplex structure if needed. For each site, we will examine recruitment patterns amongst respondents, and generate both crude point estimates for the sample recruited and population adjusted estimates of variables of interest including: women’s demographic characteristics, the proportion of women obtaining abortions from different types of providers, those experiencing complications, those seeking care etc. Additional analyses may include multivariable analyses examining the relationship between abortions with various degrees of safety or care seeking for complications and sociodemographic variables. We will also estimate the transmission rate using information on the number of respondents' close relations and the number who know about her induced abortions and its sequelae. We will measure the barrier bias by comparing the network sizes/structure of RDS respondents to that of all women in the ATPR survey.

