#### Informed consent

Informed consent will be sought from all participants (in-depth interviews, ATPR/self-report survey, RDS survey). The consent form will be read to participants and explained. The informed consent form will explain that the study is on the help of network members in case of family or reproductive problems for IDI and ATPR participants and on the safety of abortion for RDS participant. It will be made clear that the woman can stop the study at any time. The benefits (no direct benefit, see compensations below) and potential harm of the study (i.e. talk about private and potentially stressing reproductive events) will be made clear to participants. The measures taken by the study to minimize risks to the participants will be explained: how the study ensures full confidentiality and avoids accidental disclosure will be described. For participants who agree to take part in the study, informed consent will be documented as a verbal consent on a tablet.

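### The transmission and barrier factors come from an RDS list of close relations elicited under an abortion framing that the ATPR list avoids, so the corrected ATPR rate may be under-corrected by an unknown amount

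*Protocol article*

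**What the plan says.** All references are to the protocol article.

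**The hazard.** The section on the ATPR method states that "mentions of abortion in the presentation of the survey or in the network-generating question itself has been shown to inflate the estimates". The NSUM section adds that the ATPR must consider selection bias "as well as the independence of the network generating question versus the practice of interest".

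**The ATPR framing.** Under Informed consent, the study is described as concerning network help "in case of family or reproductive problems for IDI and ATPR participants and on the safety of abortion for RDS participant". ATPR respondents therefore hear a neutral description. In the ATPR questionnaire, the respondent's own reproductive history is the first section listed, but with a stated exception: "including questions on her own abortions, towards the end of the interview".

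**The RDS framing.** The same consent sentence presents the study as being "on the safety of abortion for RDS participant". The RDS questionnaire lists sociodemographics and reproductive history, then "Abortion history including number and timing of any induced abortions, how the abortion was induced (provider, setting, method" and further detail up to complications, treatment and stigma. Only then come the items meant to estimate ATPR biases, which "apply the ATPR modules to count close relations, characteristics of close relations, whether they had abortions". No deferral of the abortion history is stated.

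**Use of the RDS list.** Under Plans for analyses, transmission is estimated from the number of an RDS respondent's close relations and how many of them know of her abortion. Barrier bias is measured by "comparing the network sizes/structure of RDS respondents to that of all women in the ATPR survey". Both factors then enter the generalized NSUM model to correct the ATPR abortion rate if that is judged pertinent. Self-report is named as a possible second source of the factors. The section on respondent driven sampling expects the RDS-based factors to be the more reliable.

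**The concern.** A correction factor carries over from one survey to another only if both elicit the same kind of list. Here the same generator is used in two settings. One is a women's interview that does not mention abortion before the list is made. The other is an interview whose consent names abortion and whose listed content places a detailed abortion history ahead of the list.

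A woman thinking about her abortion will more readily name the people involved in it, and those people know about it. The share of listed relations who know would then exceed the share on a neutrally elicited list, which is the share that applies to ATPR reports. Dividing by too large a transmission rate leaves the ATPR rate too low.

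The barrier comparison has a related difficulty. A difference in network size or structure between the two surveys could be real or could come from the framing, and the design cannot tell them apart. A perfectly representative RDS sample would not help, because this is an instrument effect and not a sampling one. The planned comparison of generators uses ATPR data only, and the limitations section does not raise the issue.

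**Working it through.** **Step 1: compare the two elicitations.**

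| | ATPR survey | RDS survey |
|---|---|---|
| Topic named at consent | Network help with family or reproductive problems | Safety of abortion |
| Own-abortion questions | Stated to come late | Listed ahead of the network module; no deferral stated |
| Route into the study | Random sample of residents | Peer referral, with eligibility resting on an abortion or closeness to an abortion seeker |
| Role of the list | Source of the abortion rate | Source of the factors that correct it |

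The consent row does not depend on question order. The recruitment section places consent before the questionnaire, so abortion is named before any RDS relation is listed.

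**Step 2: direction.** The plan's warning is about inflated ATPR estimates. Extending it to transmission is an inference from the mechanism described above. For network size no direction can be inferred: a primed woman might recall additional confidantes, or might narrow her list to the few who helped.

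**Step 3: size.** The plan states no figure to reproduce, and it gives no estimate of the priming effect. What follows is illustration under assumed values. With t the transmission rate and d the ratio of close-network size (RDS over ATPR):

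corrected rate / correct rate = (t_true × d_true) / (t_used × d_used)

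Holding d fixed:

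| Assumed true t | t from primed list | Ratio |
|---|---|---|
| 0.60 | 0.70 | 0.60/0.70 = 0.86 |
| 0.60 | 0.80 | 0.60/0.80 = 0.75 |
| 0.50 | 0.55, 0.60, 0.70 | 0.91, 0.83, 0.71 |
| 0.70 | 0.75, 0.80, 0.90 | 0.93, 0.88, 0.78 |

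To see what such shifts mean, suppose that 3 of every 5 neutrally listed relations know: 3/5 = 0.60. Replacing one who does not know with one who does gives 4/5 = 0.80. If half the women make that replacement, the pooled value is 3.5/5 = 0.70.

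Now let framing also change d. With t moving from 0.60 to 0.70, a network-size ratio inflated by 10% gives 0.857/1.1 = 0.78, and one deflated by 10% gives 0.857/0.9 = 0.95. The second distortion can add to the first or offset it.

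For scale only, the sample-size section uses 48 abortions per 1,000 women for Kenya. If that were the correct rate, 48 × 0.857 = 41 and 48 × 0.75 = 36. The 48 is a published planning input, not an ATPR result.

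**Step 4: which results are affected.** If every abortion count is divided by the same overall factor c, the proportion using method m is (N_m/c)/(N/c) = N_m/N. The factor cancels, so the exposure lies in the corrected rate and in the bias estimates themselves.

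**The case against.** The strongest reply is that the article does not fix the asking order. It lists what the RDS questionnaire will include, and the ATPR questionnaire shows that listing order need not be asking order, since own abortions sit in its first section yet are asked late. The full instrument may already list relations first. This stands: a reader might infer that the plan orders the abortion history before the list, but the text supports only that it is listed first with no deferral stated. The consent contrast survives.

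Second, a reader might infer that the plan's own warning proves transmission will be overstated. It does not. It concerns inflated ATPR estimates, and neither generator in the pre-test section (important matters, shared secrets) mentions abortion. The direction for transmission is a reasonable expectation, and for network size it is open.

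Third, some priming is inherent in RDS. Women are referred by peers and consent to a study of abortion safety. Screening deliberately covers a wide range of reproductive events, but recruits who qualify have already been approached because of an abortion or because they know someone who had one. Reordering removes only an unknown part of the effect. This also stands.

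Fourth, the plan does not rest on RDS alone: the Methods strategy names self-report as a source for the factors. ATPR self-reporters answer under the neutral framing and are a built-in comparator. They are a cross-check rather than a cure, because the Background says that direct questions yield very little response in many restrictive settings, so their number may be small.

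Finally, correction of the rate is conditional, and the main purpose is abortion safety. That limits the consequence. It does not remove it, since measuring these biases is one of the stated methodological goals.

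**Conclusion.** The concern holds in a limited form. The transmission and barrier factors come from a list elicited under a different framing from the list they are meant to correct. The plan names this kind of framing as a source of bias, protects the ATPR from it, and does not say how the RDS is protected or how the difference will be handled.

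The likely consequence is an overstated transmission rate and an under-corrected abortion rate, together with a barrier comparison that mixes framing with real network differences. The size is unknown. Under the assumed values above, with network size unaffected, the corrected rate would be 0.71 to 0.93 of the correct one. That range depends on the assumed transmission rates and on the inferred mechanism. It is not a prediction.

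A reader might go further and conclude that the safety profiles are biased by this route. The documents do not support that while a single overall factor is applied to the rate. Nor do they support the view that reordering the RDS interview would make the two lists fully equivalent.

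**What to change.** 1. Specify that in the RDS interview the network generators and the full list of close relations are completed before the abortion-history block, with the same wording, order and name limit as in the ATPR. The interviewer then takes the abortion history and returns to the fixed list to ask who knows. If the full instrument already does this, say so.
2. Compare the RDS-based factors with those from ATPR self-reporters, and report the corrected rate under both. Confirm that the ATPR tool asks self-reporters which listed relations know of their abortion, because the article mentions that question only for the RDS.
3. State as a limitation that abortion-naming consent, screening and peer referral leave a residual difference between the two lists that reordering cannot remove, and that the barrier comparison should be read with that in mind.

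The cost is a reordered tablet form and one additional sensitivity analysis, with no extra participants or field staff. If the ATPR tool lacks the item on who knows, one short question is added for women who report an abortion. The reordering must be done before RDS fieldwork, because a list made after priming cannot be repaired in analysis.

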### Data management

All data collection in the main survey will be conducted on handheld android tablets using the mobile data collection software SurveyCTO collect. SurveyCTO is a platform that facilitates offline electronic data collection. Electronic data collection will be used to allow for increased security of collected data; tablets will be password-protected and completed consent forms and surveys will be uploaded to a secure server at the end of each day. Only the research team (University of Geneva and HDSS sites) will have access to the server. University of Geneva researchers will set up the secure server for the study and provide access to each site for the duration of the study.

### Plans for analyses

The analyses will focus on the two network methods applied to measure abortion safety (RDS and ATPR). The ATPR and RDS will provide data on what methods women use to have an abortion, where they have abortions and with what kind of provider, what side effects and post abortion care seeking behaviours they report.

The *RDS data* will be analyzed using the Respondent-Driven sampling analysis tool (RDSAT) or alternative tools in Stata or R, modified to take into account the multiplex structure if needed. For each site, we will examine recruitment patterns amongst respondents, and generate both crude point estimates for the sample recruited and population adjusted estimates of variables of interest including: women’s demographic characteristics, the proportion of women obtaining abortions from different types of providers, those experiencing complications, those seeking care etc. Additional analyses may include multivariable analyses examining the relationship between abortions with various degrees of safety or care seeking for complications and sociodemographic variables. We will also estimate the transmission rate using information on the number of respondents' close relations and the number who know about her induced abortions and its sequelae. We will measure the barrier bias by comparing the network sizes/structure of RDS respondents to that of all women in the ATPR survey.

Using the *ATPR data* and for each site, we will describe women’s demographic characteristics and that of their network of close relations. We will check which network-generating question yields the less selected sample of friends, and whether one question yields a sample that contains more abortion seekers, at constant characteristics. We will correct for selection bias. We will estimate the proportion of close relations obtaining abortions with different methods, different types of providers, those experiencing complications, those seeking care etc. We will do the same for women' self-reported abortions. For the ATPR point estimates, uncertainty intervals will be generated using a bootstrap or a pooled sample approach to account for the non-independence of the sample of women reported on [17]. Using the estimated transmission and barriers rates through the RDS (and perhaps self-report) and the generalized NSUM model, we will correct the ATPR estimates of the abortion rate if pertinent. We will analyze the correcting factors by socioeconomic level and stigma, to further our capacity to generalize these correction factors. We will further validate the ATPR estimates by applying ATPR to indicators drawn from the reproductive history collected for close relations and respondents (contraception), and by comparing the ATPR estimates to those from national estimates.

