### Data collection: Anonymous Third Party Reporting method

#### Sampling, inclusion criteria, and interview setting

We will conduct a cross sectional representative household-based survey among women aged 15–49. We will draw a simple random sample from the sampling frame of women 15–49 usually residing in the HDSS and randomization tables. We will use Excel to generate random numbers that will be apply to the ordered list of women in the area. The definition of residence may vary slightly across sites. To calculate sample size, we used estimates of abortion rates from published numbers in national studies or global estimates; numbers indicate a low 22 abortions per 1000 women aged 15–49 in rural Burkina Faso to a high of 48 abortions for 1000 15–49 in Kenya. The number of women aged 15–49 living in the HDSS area varies from 8500 in Nairobi to 10,000 in Kaya. Using these inputs and a random sample design, we determined that 1500 women in each site were enough to yield reliable abortion safety estimates across the two sites, assuming a reporting rate of 50% (one in two women knowing about the abortion of their close relation will report it in the survey) and two close relations. Along these assumptions, we will collect data on about 150 abortions in Kaya, and the double in Nairobi. To anticipate on possibly lower reporting rates and number of relations or abortion rates, we increase the sample size to 2000 in each site. All women^6^ who consent to participate in the study will be interviewed using the self-report/ATPR tool, in a private setting in their home or close surroundings, face to face by an interviewer recording answers on tablets.

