As in all RDS studies, each participant will receive two compensations (to be determined in accordance with local practices and national ethics committees, i.e. phone credits and/or travel expenses) for each successfully recruited additional participant. According to Heckathorn 1997, these rewards are more symbolic than substantive with studies showing that secondary compensation is particularly effective in facilitating the peer/social pressure needed to secure compliance to participate in studies within RDS networks. When participants return to the field office to receive their secondary compensation for recruiting participants, they will complete a questionnaire addressing if they tried to give coupons to other women who refused to accept it and why they were declined. All new recruits will be screened for eligibility to participate in the study after which informed consent will be taken and the questionnaire administered. They will then be trained to recruit other women and provided with coupons. The sample sizes of the RDS will be determined either during fieldwork, if saturation is reached and new respondents' characteristics are independent of those of the initial seed, or when the sample reaches a maximum of 500.

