### Limitations of the study

Despite their promise to measure abortion safety in highly restricted contexts, network-based survey approaches will inevitably miss a portion of abortions, those of women who had a direct access to the health system and those who used common-knowledge methods. However, given that information on the safety of abortion comes so far almost exclusively from hospital-based data (women who seek care after a complication, estimated at 6.9 million in 2012 that is 27% of all unsafe abortion globally) [46], the network-based sample of abortions which can be expected through network approaches (about 70–80% of all abortions in highly restrictive settings) represents a great improvement.

Moreover, while a four sites study would have been ideal (one rural and one urban site in two countries), this design is a compromise between the requests for generalization (more than one country) and budgetary constraints. Sub-Saharan Africa was chosen as the region with the highest incidence of least safe abortions.

A last concern is the reliance of the study on key informants for the formative stage and implementation of RDS. Thoughtful and purposive recruitment of these informants is key to the success of this study, since key informants who are too similar are likely to recruit women with overlapping network interactions and some parts of the networks will be missed. We outlined above the various steps taken to limit risks in this regard: the choice of Health and Demographic Surveillance Systems, whose researchers know the study populations, and the high capacity of the staff involved in fieldwork.

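### At its cap the RDS would take a large share of the eligible women (about 76% in Kaya, 41% in Nairobi), so the RDS estimator should allow for the sampling fraction

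*Protocol article*

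**What the plan says.** Under *Plans for analyses*, the RDS data "will be analyzed using the Respondent-Driven sampling analysis tool (RDSAT) or alternative tools in Stata or R", modified for the multiplex structure if needed. Crude and population-adjusted estimates are both to be produced. No estimator is named.

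RDS participants must live in the site and have had an abortion in the last 3 years. In the multiplex variant they may instead be close to someone who had one. Recruitment ends "if saturation is reached and new respondents' characteristics are independent of those of the initial seed", "or when the sample reaches a maximum of 500". Table 2 counts social referents within the 500.

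The section on ATPR sampling gives the population figures: "The number of women aged 15–49 living in the HDSS area varies from 8500 in Nairobi to 10,000 in Kaya", with "a low 22 abortions per 1000 women aged 15–49 in rural Burkina Faso" and "a high of 48 abortions for 1000 15–49 in Kenya". *Limitations of the study* expects network methods to reach "about 70–80% of all abortions in highly restrictive settings".

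The RDS questionnaire will "apply the ATPR modules to count close relations, characteristics of close relations, whether they had abortions".

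**The concern.** Inverse-degree weighting, the type associated with RDSAT, treats recruitment as sampling with replacement from a large population, so that a woman's chance of inclusion is proportional to her network size. This is a property of the method; the article does not state it. When a large part of a small population is recruited without replacement, the chance of inclusion depends much less on degree, and 1/degree weights over-correct.

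Reaching equilibrium does not cure this, and a larger sample from a fixed population makes it worse. The article nevertheless treats a large sample at equilibrium as the safeguard for representativeness.

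The RDS supplies the alternative safety estimates and the comparison for ATPR, so an error in its safety shares would enter both.

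**Working it through.** **Plan's own figure.** There is none to reproduce. The article derives neither the cap of 500 nor any sampling fraction.

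**Inputs.** Women aged 15–49: Kaya 10,000, Nairobi 8,500. Rates: 22 and 48 per 1,000, taken as annual because the period is not stated. Window: 3 years. Cap: 500 per site. Reach: 70–80%.

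**Sampling fraction** = 500 / (women × rate × 3).

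- Kaya: 10,000 × 0.022 × 3 = 660; 500/660 = 75.8%.
- Nairobi: 8,500 × 0.048 × 3 = 1,224; 500/1,224 = 40.8%.

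**How the fraction moves** (the shares and Kaya rates in the first three rows are assumptions):

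| Change | Kaya | Nairobi |
|---|---|---|
| Half of the 500 are seekers (250/N) | 38% | 20% |
| Kaya rate 35 or 48 per 1,000 (N = 1,050 or 1,440) | 48% or 35% | – |
| 10% of abortions are repeats (N = 594; 1,102) | 84% | 45% |
| Reach 70–80% (N = 462–528; 857–979) | 108–95% | 58–51% |

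**Effect on a safety share.** Successive sampling without replacement, with probability proportional to degree, was simulated with a true share of 40% and n = 500, all seekers. In setting A, degree is 1 + Poisson, with Poisson mean 4 in the other women and 4 × ratio in the group of interest. In setting B, mean degree is 3 in the other women. Degree levels and ratios are assumptions in both. Results are for ratios 1.5 / 2.

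| | Inverse-degree, A | Inverse-degree, B | Successive sampling, correct N (A; B) |
|---|---|---|---|
| Kaya, N = 660 | 35.5 / 32.0% | 34.5 / 30.5% | 40.0 / 40.0%; 40.1 / 39.9% |
| Nairobi, N = 1,224 | 38.0 / 36.7% | 37.6 / 36.0% | 39.9 / 40.2%; 39.9 / 40.5% |
| N = 20,000 | 40.0 / 39.7% | – | 40.1 / 39.9% (A) |

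The bias disappears at N = 20,000, so the sampling fraction is the cause. At ratio 1 it also disappears: in setting A, 40.1% in Kaya and 39.9% in Nairobi. At ratio 0.5 it reverses: 46.9% and 42.5%. If half the recruits are seekers, the error at ratios 1.5 to 2 falls to about 2–4 points in Kaya and 1–2 in Nairobi.

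**What a wrong N does.** With a true N of 1,440 and an assumed N of 660, successive sampling gives 43.5 / 46.1% against 37.9 / 36.3% for inverse-degree. The errors are 3.5 / 6.1 points against 2.1 / 3.7, so the finite-population estimator is then the worse one.

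**The case against.** The strongest reply is that the plan fixes no estimator. It allows alternative tools in Stata or R, which can include successive sampling, and a condensed article may leave the choice to an analysis plan that is not shown. This stands. A reader might infer that the RDS safety shares will be biased; the article supports only that they would be if inverse-degree weights were used and degree were related to safety.

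The fractions are also not fixed quantities. The 500 is a maximum with an earlier stop at saturation, and it may include social referents. The rate of 22 per 1,000 is for rural Burkina Faso, while the Kaya site has urban formal and informal settlements, so 660 is not an upper limit. Both points stand, but the cases worked above still give 20% or more.

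Three further inferences should not be drawn:

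- **That the questionnaire has no measure of degree.** The ATPR modules record relations' abortions in the past 3 years and whether they live in the area, so seekers among close relations can be counted. Only a count beyond close relations is absent.
- **That the Kaya sample size is wrong.** It is a cap with a saturation stop. It may simply not be attained.
- **That the ATPR corrections are shown to be biased by the amounts above.** The table concerns safety shares only, and the correction applies to the abortion rate, if pertinent.

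Finally, crude estimates are planned too. In setting A they err in the opposite direction (Kaya 43.5 / 45.9%), so a wide gap between crude and weighted results would give some warning.

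**Conclusion.** The point holds as a conditional one. At the cap, with every recruit a seeker, the RDS would take about 76% of recent seekers in Kaya and 41% in Nairobi on the plan's own inputs. With half the recruits referents, or a higher Kaya rate, the fraction is still between 20% and 48%.

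Under inverse-degree weighting the error in a 40% safety share is roughly 1 to 9 points at degree ratios of 1.5 to 2, larger in Kaya than in Nairobi, and zero if degree and safety are unrelated. The fractions assume annual rates. The size of the bias rests on degree values that the documents do not give. This is a worthwhile and inexpensive improvement to the plan; it does not show that the planned estimates are invalid.

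**What to change.** - **Estimator.** In *Plans for analyses*, name a successive-sampling (Gile SS) estimator with its finite-population bootstrap as the main RDS estimator. Report the inverse-degree and crude estimates beside it. Apply the weights to abortion seekers only.
- **Population size.** Take N from the HDSS count of women, the site abortion rate and the 3-year window, including a version that uses the study's own ATPR-based count. Run sensitivity analyses in both directions. For Kaya, go for example from the number of seekers actually recruited up to about 1,440. Do not fix N at 660, and do not set it below the achieved sample: 500 women cannot be drawn from 462.
- **Questionnaire.** Add one item: how many women aged 15–49 living in the area the respondent knows to have had an abortion in the last 3 years.
- **Cap.** Note that on the rural rate and 70–80% reach, about 460–530 seekers in Kaya are reachable, so 500 may not be attained there.

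The cost is a few lines of analysis text, free R software and one question. The question must be settled before fieldwork because it cannot be recovered later. The drawback is that results then depend on an assumed N, and a wrong N can bias them either way; this is why the sensitivity runs must be two-sided.
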